### Sample size calculation

It is planned that up to 1200 participants will be enrolled. This sample size was calculated based on an assumed number of model parameters of 22 to 24, an assumed prevalence of RA-ILD in the study population (which is enriched for patients with RA-ILD) of 30%, an assumed c-statistic for the model of 0.75, and an assumed shrinkage factor associated with the predictors of 0.9 [52]. In this setting, the number of events per predictor parameter would be 15. A difference of 0.05 between the apparent and adjusted R^2^ of the model and a margin of error of 0.05 in estimating the risk of RA-ILD when the coefficients for all candidate predictors are set to zero is expected. After HRCT results from the first 600 participants are available, an interim analysis will be performed to determine whether the prevalence of RA-ILD in the study population will enable the modelling based on risk factors or if the sample size needs to be adjusted.

### Ultrasound sub-study

To investigate the performance of lung ultrasound in detecting ILD compared to HRCT, including predictive values, sensitivity and specificity, a sub-study will be conducted at sites where rheumatologists have been trained on bedside lung ultrasound. A standardised approach to ultrasound probe, anatomical location and data collection will be provided. Images will be taken from 14 areas. The measures analysed will include the total number of B lines, pleural thickness (normal/abnormal), pleural regularity (normal/irregular) and the presence/absence of pleural effusion and consolidation. It is not intended that sites will refer participants to radiology for formal ultrasonographic assessment.

## Discussion

The data collected in the ANCHOR-RA study will establish the prevalence of RA-ILD in a high-risk population and enable development of a multivariable model for prediction of RA-ILD. This model will be based on risk factors that are easily assessed in clinical practice, which can be used to decide which patients with RA should be screened for ILD using HRCT. Risk scores developed in previous studies have shown good specificity and sensitivity for the identification of patients with RA-ILD [32, 53–57]. However, these risk scores were developed in small or single-centre populations [32, 53–56] and some were based on patients with known ILD [53, 57] or in patients referred for HRCT because ILD was suspected [56]. A risk score developed based on sex, smoking status, CDAI, ESR and extra-articular manifestations in 118 patients with RA had 90% sensitivity and 64% specificity for identifying patients with RA-ILD on HRCT [53], while a risk score developed based on sex, age at RA onset, DAS-28-ESR score and the *MUC5B* promoter variant in 163 patients with RA had 75% sensitivity and 85% specificity [32]. A risk score developed based on age at RA onset, smoking status, RF titre, CCP titre and DAS-28 score in 430 patients with RA had 86% sensitivity and 58% specificity for identifying patients with RA-ILD on HRCT [56]. A nomogram developed using data on sex, smoking status, RF, CRP and matrix metalloproteinase-3 from 223 patients at a single centre had a c-index of 0.826 for identification of RA-ILD compared with an assessment by a multidisciplinary team [55]. We seek to build on these studies by developing a risk score for RA-ILD that could easily be applied in clinical practice. The results of the ANCHOR-RA study will also elucidate the prevalence of RA-ILD in patients with particular risk factors. Understanding the prevalence of RA-ILD in sub-populations of patients with RA is important given its significant impact on prognosis [4, 7–11] and the burden that it places on healthcare resources [58].

The most frequent radiological patterns seen in patients with RA-ILD are usual interstitial pneumonia (UIP) and non-specific interstitial pneumonia (NSIP) [4, 59–61]. A UIP pattern on HRCT has been associated with worse survival in patients with RA-ILD [62–64]. Greater extents of fibrosis, traction bronchiectasis, honeycombing, and reticulation, and the presence of emphysema, have also been associated with worse survival [60, 64–66]. The ANCHOR-RA study will provide further data on the prevalence of these features on HRCT in patients with RA-ILD.

Early diagnosis of RA-ILD provides the opportunity to improve its monitoring and management. The course of RA-ILD is variable, with some patients experiencing rapid progression while others remain relatively stable [67, 68]. Progressive pulmonary fibrosis in patients with RA-ILD is characterised by increasing radiological fibrosis, decline in lung function, worsening symptoms, and early mortality [67, 69, 70]. Early detection of RA-ILD, and of its progression, enables treatment to be initiated promptly. Data from retrospective or uncontrolled studies suggest that immunosuppression may slow the progression of RA-ILD [71–74], but in the absence of randomised controlled trials, the effect of these therapies remains unclear. Based on the results of the randomised placebo-controlled INBUILD trial [75], the tyrosine kinase inhibitor nintedanib has been licensed for the treatment of progressive fibrosing ILDs of any aetiology and was given a conditional recommendation for use in patients with progressive pulmonary fibrosis who have failed standard management for fibrotic ILD in a clinical practice guideline [22]. Data from the subgroup of patients with progressive fibrosing RA-ILD in the INBUILD trial provide further support for its use in these patients [76].

Strengths of the ANCHOR-RA study include that it is large and multi-national, that consecutive recruitment of patients will minimise the risk of bias (e.g. investigators preferentially putting forward patients suspected to have ILD), and that a wide range of clinical and lung imaging data will be collected. Limitations include that the results will be applicable only to patients with RA who have the specified risk factors for ILD.

In conclusion, the results of the multi-national cross-sectional ANCHOR-RA study will enable the development of a probability score for RA-ILD based on a multivariable model incorporating risk factors and will elucidate the prevalence of RA-ILD in patients with multiple risk factors. These data will add to the body of evidence that will support recommendations for screening for RA-ILD to improve detection of this important complication of RA and enable early intervention.

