**Methods:**

Investigators will enrol consecutive patients with RA who have ≥ 2 of the following risk factors for RA-ILD: male; current or previous smoker; age ≥ 60 years at RA diagnosis; high-positive rheumatoid factor and/or anti-cyclic citrullinated peptide (titre > 3 x upper limit of normal); presence or history of certain extra-articular manifestations of RA (vasculitis, Felty’s syndrome, secondary Sjögren’s syndrome, cutaneous rheumatoid nodules, serositis, and/or scleritis/uveitis); high RA disease activity in the prior 12 months. Patients previously identified as having ILD, or who have had a CT scan in the prior 2 years, will not be eligible. Participants will undergo an HRCT scan at their local site, which will be assessed centrally by two expert radiologists. Data will be collected prospectively on demographic and RA-related characteristics, patient-reported outcomes, comorbidities and pulmonary function. The primary outcomes will be the development of a probability score for RA-ILD, based on a multivariable model incorporating potential risk factors commonly assessed in clinical practice, and an estimate of the prevalence of RA-ILD in the study population. It is planned that 1200 participants will be enrolled at approximately 30 sites in the USA, UK, Germany, France, Italy, Spain.

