## Methods/design

### Study design and participants

The ANCHOR-RA study is a cross-sectional study that will be conducted at approximately 30 sites in the USA, UK, Germany, France, Italy, Spain. Eligible patients will be diagnosed with RA according to the 1987 American College of Rheumatology (ACR) [37] or the 2010 ACR/European Alliance of Associations for Rheumatology (EULAR) [38] classification criteria, with any duration of RA, and have ≥ 2 of the following risk factors for RA-ILD: male; current or previous smoker; age ≥ 60 years at RA diagnosis; high-positive RF and/or anti-CCP (titre > 3 x upper limit of normal); presence or history of certain extra-articular manifestations of RA (vasculitis, Felty’s syndrome, secondary Sjögren’s syndrome, cutaneous rheumatoid nodules, serositis, and/or scleritis/uveitis); high RA disease activity in the prior 12 months (Table 1). Patients will be excluded if they have previously been identified as having ILD, have had a chest CT in the prior 2 years, have received treatments known to induce ILD (e.g. radiation therapy to chest, bleomycin), have had a lung transplant, or have been diagnosed with an autoimmune disorder overlapping with RA, except secondary Sjögren’s syndrome. There is no restriction on the use of disease-modifying antirheumatic drugs (DMARDs).

**Table 1 Tab1:** Disease activity measures used to ascertain high RA disease activity in the ANCHOR-RA study

Measure	Range	High RA disease activity
PAS score [39]	0 to 10	≥ 8.0 to ≤ 10.0
PAS-II score [39]	0 to 10	≥ 8.0 to ≤ 10.0
RAPID-3 score [40]	0 to 10	> 4 to ≤ 10
CDAI score [41]	0 to 76	> 22.0
DAS-28-ESR or DAS-28-CRP [42, 43]	0 to 9.4	> 5.1
SDAI score [44]	0 to 86	> 26

CDAI, Clinical Disease Activity Index; DAS-28-ESR, Disease Activity Score with 28 joints using erythrocyte sedimentation rate; DAS-28-CRP, Disease Activity Score with 28 joints using C-reactive protein; PAS, Patient Activity Scale; RA, rheumatoid arthritis; RAPID-3, Routine Assessment of Patient Index Data 3; SDAI, Simple Disease Activity Index

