### Outcomes

The primary outcomes will be the development of a probability score for RA-ILD, based on a multivariable model incorporating potential risk factors commonly assessed in clinical practice, and an estimate of the prevalence of RA-ILD and of radiological features of RA-ILD on HRCT in the study population.

Secondary outcomes will be the demographic and disease characteristics of participants with RA who do and do not have respiratory symptoms (cough and/or dyspnoea), the performance of the model in sub-populations with and without cough and/or dyspnoea, and correlations of pulmonary function tests and abnormal findings on auscultation with findings on HRCT.

Further outcomes include a multivariable model that additionally considers the *MUC5B* promoter variant as a potential predictor of RA-ILD. The performance of the model to predict RA-ILD defined using different extents of ILD and patterns on HRCT will be assessed in sensitivity analyses. The prevalence and HRCT features of free-standing bronchiectasis and emphysema will also be assessed.

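### The prevalence outcome measures previously unidentified ILD, but the article presents it as the prevalence of RA-ILD in high-risk patients

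*Protocol article*

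**What the plan says.** Under Study design and participants, the article states: "Patients will be excluded if they have previously been identified as having ILD, have had a chest CT in the prior 2 years". The abstract's Methods paragraph gives the same two exclusions.

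Under Outcomes, one of the primary outcomes is "an estimate of the prevalence of RA-ILD and of radiological features of RA-ILD on HRCT in the study population".

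Elsewhere the result is described more broadly. The last paragraph of the Background gives the aim as evaluating prevalence in patients who have risk factors. The opening paragraph of the Discussion says the study "will establish the prevalence of RA-ILD in a high-risk population" and, further on, that its results "will also elucidate the prevalence of RA-ILD in patients with particular risk factors". The concluding paragraph repeats the claim for patients with several risk factors. None of these places says that known cases are absent.

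The strengths and limitations paragraph of the Discussion says: "Limitations include that the results will be applicable only to patients with RA who have the specified risk factors for ILD". It does not mention the two exclusions.

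**The concern.** Patients with diagnosed ILD leave both the numerator and the denominator. What remains is the yield of HRCT in patients not known to have the disease. That is a useful quantity for deciding whom to screen, but it is not the prevalence of RA-ILD in the risk-factor population.

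The difference matters because prevalence is a primary outcome, and the Discussion justifies it by the effect of RA-ILD on prognosis and on healthcare resources. Both concern all RA-ILD, diagnosed cases included. The Background notes that published estimates run from 2% to 41% depending on the population and the definition of ILD, so a misdescribed population would add to that spread. The planned data on HRCT features will likewise describe only cases that had not been identified before.

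**Working it through.** **The plan's own figure.** The sample size section assumes 30% prevalence in the study population, up to 1200 participants, 22 to 24 parameters and 15 events per parameter. 1200 × 0.30 = 360 events, and 360 / 24 = 15.0. The figure reproduces.

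**Sampling error.** The 95% half-width at N = 1200 and p = 0.30 is 1.96 × √(0.30 × 0.70 / 1200) = 0.026, or 2.6 points.

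**Known-ILD exclusion.** Let t be the total prevalence among patients who meet the risk-factor rule, and d the share of those cases already known. Removing known cases from numerator and denominator gives

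study prevalence = t(1 − d) / (1 − td).

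The article gives neither t nor d. With t = 0.30 assumed for illustration:

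| d (assumed) | Calculation | Study prevalence | Shortfall from 30% |
|---|---|---|---|
| 10% | 0.270 / 0.970 | 27.8% | 2.2 points |
| 25% | 0.225 / 0.925 | 24.3% | 5.7 points |
| 50% | 0.150 / 0.850 | 17.6% | 12.4 points |

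The sign does not depend on the choice of values: for any d above 0 and t between 0 and 1, the result is below t.

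**The reverse direction.** If 30% is the prevalence in the study population, as the sample size section states, the total is t = 0.30 / (1 − d + 0.30d):

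- d = 10%: 0.30 / 0.930 = 32.3%
- d = 25%: 0.30 / 0.825 = 36.4%
- d = 50%: 0.30 / 0.650 = 46.2%

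**Recent-CT exclusion.** Let c1 and c0 be the shares removed by this rule among patients with unidentified ILD and without ILD. Then

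study prevalence = t(1 − d)(1 − c1) / [t(1 − d)(1 − c1) + (1 − t)(1 − c0)].

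With t = 0.30 and d = 25% (rates all assumed):

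- c1 = c0 = 10%: 24.3%, no further change.
- c1 = 30%, c0 = 10%: 0.1575 / (0.1575 + 0.630) = 20.0%, a further fall.
- c1 = 10%, c0 = 30%: 0.2025 / (0.2025 + 0.490) = 29.2%, a rise.

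The article does not say why patients were scanned or what the scans showed, so the direction cannot be determined.

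**The case against.** The strongest reply is that the outcome is formally correct. The abstract and the Outcomes section both refer to the study population, and the exclusions are disclosed. They also fit the purpose: a model for choosing whom to screen should be built in patients not known to have ILD, and the Discussion faults some earlier scores for relying on known cases. All of this stands. The fault lies in how the estimate is described, not in the design. But a correct formal definition does not cure an aim, a Discussion and a conclusion that all name a broader quantity.

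The limitation sentence is also not worded as a complete list. That is fair, but it is the only statement on applicability, and it leaves out the restriction that most directly affects a prevalence.

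The assumed known shares have no source in the article. At 10% the shift of 2.2 points is inside the 2.6-point half-width. This limits what can be said about size, not direction.

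A reader might infer three stronger points, which the article does not support:

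- **That the study is too small.** Treating 30% as total prevalence and applying the exclusions would cut events per parameter from 15 to 12.2 or 8.8 (d = 25% or 50%). But the plan gives "an assumed prevalence of RA-ILD in the study population (which is enriched for patients with RA-ILD) of 30" per cent, which already refers to participants after exclusions. An interim analysis after 600 HRCT results also checks whether prevalence permits the modelling or the sample size needs adjusting.
- **That the sample is depleted of ILD, so calling it enriched is wrong.** Selecting on at least 2 risk factors may well leave it enriched relative to RA in general.
- **That the recent-CT rule biases the estimate downward.** Patients whose scan identified ILD are already excluded as known cases. Those removed by the CT rule alone had a scan that did not lead to ILD being identified, so removing them could raise the estimate.

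**Conclusion.** The point stands as a misdescription of a primary estimate. The design measures previously unidentified ILD in patients with RA, at least 2 risk factors and no chest CT in the prior 2 years. The article says it will establish the prevalence of RA-ILD in high-risk patients.

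The known-ILD exclusion is enough to support this. It puts the estimate below total prevalence whenever any case is already known, by 2.2, 5.7 or 12.4 points under the illustrative assumptions (total 30%; 10%, 25% or 50% known). At 25% and 50% the shift exceeds the sampling error, and no increase in N removes it. The recent-CT exclusion narrows the population further, with unknown direction and size. Neither the exclusions nor the sample size needs to change, but what the study may conclude about prevalence does.

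**What to change.** 1. In the Background aim, the Outcomes section and the opening and concluding paragraphs of the Discussion, describe the estimate as the prevalence of previously unidentified ILD in patients with RA, at least 2 risk factors, no known ILD and no chest CT in the prior 2 years.
2. Add both exclusions to the limitation in the Discussion, and say that the estimate is expected to be lower than total prevalence if some cases are already known.
3. As a supplement, count during consecutive screening the patients with at least 2 risk factors who are excluded for known ILD, excluded for recent CT, or who decline. Report these counts beside the estimate, noting that known cases were not centrally adjudicated and so cannot simply be pooled with cases found by the study's HRCT reading.

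Items 1 and 2 cost only wording and a narrower claim. Item 3 needs a few entries per screened patient and is best set up prospectively, since such counts are hard to recover after enrolment. If the full protocol already provides such a log, only the reporting needs to be added.

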## Data Availability

Not applicable (No data are provided in this manuscript).

## Abbreviations

AA-VAS: Arthritis Activity Visual Analogue Scale
ACR: American College of Rheumatology
CCP: cyclic citrullinated peptide
CDAI: Clinical Disease Activity Index
CRP: C-reactive protein
CT: computed tomography
DAS-28: Disease Activity Score with 28 joints
DAS-28-CRP: Disease Activity Score with 28 joints using C-reactive protein
DAS-28-ESR: Disease Activity Score with 28 joints using erythrocyte sedimentation rate
DLco: Diffusing capacity of the lung for carbon monoxide
DMARDs: Disease-modifying antirheumatic drugs
ESR: Erythrocyte sedimentation rate
EULAR: European alliance of associations for rheumatology
FEV< _1_: Forced expiratory volume in one second
FVC: Forced vital capacity
HRCT: High-resolution computed tomography
ILD: Interstitial lung disease
L-PF: Living with pulmonary fibrosis
MDHAQ: Multidimensional health assessment questionnaire
mMRC: modified Medical Research Council
NSIP: Non-specific interstitial pneumonia
PAS: Patient activity scale
RA: Rheumatoid arthritis
RAPID-3: Routine assessment of patient index data 3
RF: Rheumatoid factor
SDAI: Simple disease activity index
SF-36: 36-Item short form survey
UIP: Usual interstitial pneumonia
VAS: Visual analogue scale
